## Abstract

**Background:**

Chronic obstructive pulmonary disease (COPD) is one of the most common disorders in the world. COPD is characterized by airflow obstruction, which is not fully reversible. Patients usually experience breathing-related symptoms with periods of acute worsening and a substantial decrease in the health-related quality-of-life. Active and comprehensive disease management can slow down the progressive course of the disease and improve patients’ disabilities. Technological progress and digitalization of medicine have the potential to make elaborate interventions easily accessible and applicable to a broad spectrum of patients with COPD without increasing the costs of the intervention.

**Objective:**

This study aims to develop a comprehensive telemonitoring and hybrid virtual coaching solution and to investigate its effects on the health-related quality of life of patients with COPD.

**Methods:**

A monocentric, assessor-blind, two-arm (intervention/control) randomized controlled trial will be performed. Participants randomized to the control group will receive usual care and a CAir Desk (custom-built home disease-monitoring device to telemonitor disease-relevant parameters) for 12 weeks, without feedback or scores of the telemonitoring efforts and virtual coaching. Participants randomized to the intervention group will receive a CAir Desk and a hybrid digital coaching intervention for 12 weeks. As a primary outcome, we will measure the delta in the health-related quality of life, which we will assess with the St. George Respiratory Questionnaire, from baseline to week 12 (the end of the intervention).

**Results:**

The development of the CAir Desk and virtual coach has been completed. Recruitment to the trial started in September 2020. We expect to start data collection by December 2020 and expect it to last for approximately 18 months, as we follow a multiwave approach. We expect to complete data collection by mid-2022 and plan the dissemination of the results subsequently.

**Conclusions:**

To our knowledge, this is the first study investigating a combination of telemonitoring and hybrid virtual coaching in patients with COPD. We will investigate the effectiveness, efficacy, and usability of the proposed intervention and provide evidence to further develop app-based and chatbot-based disease monitoring and interventions in COPD.

**Trial Registration:**

ClinicalTrials.gov identifier: NCT04373070; https://clinicaltrials.gov/ct2/show/NCT04373070

**International Registered Report Identifier (IRRID):**

DERR1-10.2196/20412

## Introduction

### Background

Chronic obstructive pulmonary disease (COPD) is a chronic lung disease commonly caused by exposure to noxious particles (primarily from smoking) and characterized by respiratory symptoms (ie, dyspnea, cough, and sputum) and airflow obstruction [1]. Patients experience persistent respiratory symptoms with periods of acute worsening (exacerbations) and a substantial decrease in health-related quality of life (HRQOL). In 2016, about 251 million people worldwide were affected by COPD [2]*.* COPD is projected to become the third-leading global cause of death by 2030 [3]. In addition to the health implications, COPD causes a substantial economic burden on the individual and the health care systems [4]. There is no cure for COPD. However, effective treatment such as medication, smoking cessation, and physical exercise helps to relieve symptoms and prevent exacerbations [5]. Active disease management to reduce the burden of COPD and improve HRQOL therefore plays a crucial role in the therapeutic strategy.

Effective COPD management plans follow a patient-centered approach and aim to (1) prevent disease progression through the reduction of risk factors, (2) improve exercise tolerance, (3) improve health status, and (4) relieve symptoms [5]. Best practice treatment of COPD should be multidimensional and include medical care, self-management strategies, physical activity coaching, and behavioral change approaches [6-8]. One of these evidence-based disease management programs is *Living well with COPD* [9,10]. The program was developed by a Canadian consortium and is based on a disease self-management approach that covers educational topics as well as lifestyle coaching and physical activity advice supervised by health care professionals [9]. A randomized clinical trial showed that compared to usual care in a multicenter setup, the *Living well with COPD* intervention program reduced hospital admissions due to COPD exacerbations, emergency department visits, and unscheduled physician visits and improved HRQOL significantly [9]. A recent clinical trial conducted in Switzerland confirmed these results [8]. The implementation of the program, however, is both time and cost intensive.

Technological progress and the digitalization of medicine have the potential to make comprehensive interventions such as the *Living well with COPD* program easily accessible and applicable to a broad spectrum of patients with COPD without increasing the costs of the intervention. Prior research has proven the effectivity and efficiency of novel treatment solutions that incorporate telemonitoring and virtual coaching [11]. To our knowledge, however, no clinical trial has been conducted with a multimodal intervention based on the concept of *Living well with COPD* that is delivered remotely.

To fill this gap in research, we, a consortium between IBM Research, docdok.health, the University Hospital Zurich, and the Swiss Federal Institute of Technology developed a comprehensive telemonitoring and hybrid virtual coaching solution called CAir, which is based on the *Living well with COPD* program, and will investigate its effects on the HRQOL in patients with COPD.

### Hypotheses

The primary outcome of this study is the assessment of patients’ change in HRQOL, which we will evaluate with the St. George Respiratory Questionnaire (SGRQ) [12], a survey specifically designed for patients with chronic airflow limitations. A minimal clinically important difference of an average SGRQ score decrease of 4 units is associated with a slightly effective intervention, 8 units with a moderately effective intervention, and 12 units with a very effective intervention in patients with COPD [13].

Against this backdrop and considering the comprehensiveness of CAir, the hypotheses of this study are as follows:

More than 80% of the intervention group will have a ≥4-point change in SGRQ.More than 40% of the intervention group will have a ≥8-point change in SGRQ.More than 20% of the intervention group will have a ≥12-point change in SGRQ.Approximately 10% of the control group will have a ≥4-point change in SGRQ.

We formulated the fourth hypothesis based on the Hawthorne effect [14], which states that individuals change their behaviour when they know they are being observed. This assumption is further supported by several studies in which the mean HRQOL within the control group also increased in a clinically relevant manner without any intervention [15].

## Methods

We will perform a monocentric, assessor-blind, two-arm (intervention/control) randomized controlled trial. The allocation ratio between the intervention and control group will be 2:1. Bias will be minimized through randomization, allocation concealment, assessor blinding, and statistical adjustment or subgrouping during the analysis. The study is expected to have an overall duration of 18 months (first patient in, last patient out). The length of study per patient will be 12 weeks. The recruitment period will last several months.

### Participants

#### Eligibility Criteria

Participants will be recruited from the Swiss population affected by COPD. Inclusion and exclusion criteria are outlined in Textbox 1.

Inclusion and exclusion criteria and re-screening for the CAir study.
**Inclusion criteria:**
Provision of written informed consentAge≥40 yearsAbility to speak German fluentlyDiagnosis of chronic obstructive pulmonary disease according to the Global Initiative for Chronic Obstructive Lung Disease guidelines
**Exclusion criteria:**
Physical or intellectual impairment precluding informed consent or protocol adherenceAcute or recent (within the last 6 weeks) exacerbation of chronic obstructive pulmonary diseaseAttending a pulmonary rehabilitation program within the last 3 monthsOngoing pregnancy
**Re-screening**
In case of an exacerbation less than 6 weeks prior to the study or completing a pulmonary rehabilitation less than 3 months previous to the study, patients can be included with a delay to ensure eligibility

#### Recruitment, Screening, and Informed Consent Procedure

Participants will be recruited directly from the outpatient clinic of the Department of Pulmonology of the University Hospital Zurich by a physician or study coordinator involved in the care, and indirectly by screening the hospital’s patient database for the eligibility and ineligibility criteria (Textbox 1). In case patients meet the criteria, they will be contacted by a letter of enquiry that contains a study information sheet and a prestamped reply envelope. Those indicating interest in taking part in the study will be contacted by phone. In addition, cooperating pulmonary clinics and primary care physicians will equally screen their databases for patients fulfilling the main inclusion criteria (ie, diagnosis of COPD and age ≥40 years) and will send them study participation requests. Interested patients will then independently contact the study team of the University Hospital Zurich, which will evaluate the remaining inclusion and exclusion criteria.

We will not offer any material compensation for participating in this study. Potential participants will be informed about the scientific benefit of their participation; however, no other incentives will be offered.

All patients will be required to provide written informed consent before starting the trial. In that context, investigators will educate each participant about the nature of the study, its purpose, procedures involved, expected duration, potential risks and benefits, and any possible discomfort. Patients will also be informed that their participation is strictly voluntary and that they can withdraw from the study at any time without stating any reason. They will also be informed that withdrawing from the study will not affect subsequent medical assistance and treatment. The participants will be further advised that their medical records may be examined by authorized individuals other than their treating physician. Participants will be given sufficient time to reflect extensively on their participation.

The consent form will be signed and dated by the investigator or designee immediately following the signature of the participant. The consent form will be retained as part of the study records. A signed copy will be provided to each study participant.

#### Sample Size

Sample size calculations used a power of 80% and a two-sided significance level of 0.05. To increase usability reporting and account for possible dropouts, we decided to use a 2:1 (intervention:randomization) ratio and doubled the result of the sample size calculation. The sample size calculation yielded a total of 42 patients (28 intervention, 14 control). This sample size will result in an effect size of 0.9 to detect a clinically relevant between-group difference in the SGRQ.

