### Strengths and Limitations

Randomized controlled trials are considered the “gold standard for evaluating efficacy in clinical research and constitute evidence for medical treatment” [25]. By adopting such a trial and ensuring internal as well as external validity, we maximize the robustness of our study. To make sure that the CAir Desk will function well with the study population, we extensively pretested the device in patients with COPD. The technology we used as part of the CAir Desk is well established and not likely to malfunction in daily use. A possible limitation is that the intervention is rather technology-heavy and the study population includes persons aged 45 years and older. Even though we pretested the system usability extensively in patients with COPD from the same population, some participants might feel overwhelmed and therefore discontinue the study. In addition, patients may feel overloaded by the daily measurements and questionnaires to be answered, which could also lead to dropouts. Another possible limitation is the limited size of the sample, given the heterogeneity in the population affected by COPD.

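### The sample-size paragraph credits the doubling and the 2:1 ratio with covering dropouts, but its effect size of 0.9 at 80% power needs all 42 patients evaluable

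*Protocol article*

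**What the plan says.** The Sample Size section opens with the design values: "Sample size calculations used a power of 80% and a two-sided significance level of 0.05". It gives two reasons for what follows, better usability reporting and allowance for dropouts, and on those grounds "we decided to use a 2:1 (intervention:randomization) ratio and doubled the result of the sample size calculation". The next sentence reads "The sample size calculation yielded a total of 42 patients (28 intervention, 14 control", and the last one says "This sample size will result in an effect size of 0.9 to detect a clinically relevant between-group difference in the SGRQ". The Methods section confirms the ratio: "The allocation ratio between the intervention and control group will be 2:1".

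The section gives no size before doubling, no SGRQ difference in points, no standard deviation and no dropout rate. The Statistical Analysis section plans an independent-samples t test for the primary endpoint, with multiple imputation for data missing at the baseline and final visits. Strengths and Limitations acknowledges that "some participants might feel overwhelmed and therefore discontinue the study", and names the daily measurement burden as a second possible cause of dropout.

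**The concern.** Two statements in the paragraph do not fit together.

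First, the extra patients are said to be there partly for dropouts. An allowance for dropouts should leave the stated power intact after some patients are lost. Here the effect size is attached to the whole sample of 42, so the allowance has already been spent on reaching 0.9.

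Second, 42 is called the yield of the calculation, while the sentence before says that the yield was doubled. The number cannot be both the result and twice the result, and the paragraph does not say which it is.

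What is at stake is how a null or borderline primary result would be read. A reader would take the trial to have 80% power for 0.9 SD with dropout already provided for. For the SGRQ mean comparison that provision is not there.

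**Working it through.** **Inputs.** Two-sided alpha 0.05, power 80%, standardised effect d = 0.9, and arms of 28 and 14, all from Sample Size. The two-sample t test is from Statistical Analysis. Dropout of 5% to 20%, equal in both arms, is an assumption because the documents give no rate.

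**Formulas.** With arms n1 and n2, let k = n1·n2/(n1+n2). Power is the probability that a noncentral t variable with n1+n2−2 degrees of freedom and noncentrality d·√k exceeds the two-sided 5% critical value. The normal approximation is Φ(d·√k − 1.960). The effect detectable with 80% power is the d that makes power 0.80; by normal approximation it is (1.960 + 0.842)/√k.

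**Step 1: the plan's own figure.** For 28:14, k = 392/42 = 9.33 and √k = 3.055.
- Detectable effect at 80% power: 0.917 by normal approximation (2.802/3.055), 0.940 by exact t test. Both round to 0.9, so the stated figure is reproduced.
- Power at d = 0.9 exactly: noncentrality 0.9 × 3.055 = 2.750. Exact t test 76.5%; normal approximation Φ(0.790) = 78.5%.

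The figure is reproduced only with all 42 patients in the analysis.

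**Step 2: losing patients.** Exact t test, arms 28(1−q) and 14(1−q):

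| Assumed dropout q | Arms | Power at d = 0.9 | Detectable effect, 80% power |
|---|---|---|---|
| 0% | 28 : 14 | 76.5% | 0.94 |
| 5% | 26.6 : 13.3 | 74.3% | 0.97 |
| 10% | 25.2 : 12.6 | 71.8% | 0.99 |
| 15% | 23.8 : 11.9 | 69.2% | 1.02 |
| 20% | 22.4 : 11.2 | 66.4% | 1.06 |

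**Step 3: does the 2:1 ratio add reserve?** At a fixed total of 42, k is 9.33 for 28:14 and 441/42 = 10.5 for 21:21. The ratio 9.33/10.5 = 0.889 is the relative efficiency. Unequal allocation therefore costs about 11% of the information. It may serve usability reporting, but it does not offset dropout.

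**Step 4: which figure was doubled?** Both readings, at d = 0.9:
- 42 is the doubled figure. The base is 21 (14:7), with 45% power and a detectable effect of 1.37 SD. The base calculation then cannot have targeted 0.9 at 80% power.
- 42 is the figure before doubling. The trial would enrol 84 (56:28), with 97% power and a detectable effect of 0.66 SD. That contradicts the attachment of 0.9 to the final sample.

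Neither reading gives a calculation for 0.9 that was then doubled to 42.

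**The case against.** **The shortfall with complete data is rounding.** This stands. The paragraph gives the sample size as input and the effect size as output, to one decimal. Since 0.917 and 0.940 both round to 0.9, a reader who solves back from exactly 0.900 and concludes that the plan misses its 80% power is reading more precision into 0.9 than it carries.

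**A 1:1 calculation is not shown.** A reader might infer that 42 came from equal allocation, because 21 per arm gives 81.2% power at 0.9. But 28:14 also gives 0.9 at the stated precision, and the documents state 2:1 throughout. The inference is not supported, and nothing here depends on it.

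**The doubling may be a reserve for another target.** The Hypotheses section expects more than 80% of the intervention group and about 10% of controls to change by at least 4 points. At 80% against 10%, 2:1 allocation and a continuity correction, the calculation gives 7 controls and 14 intervention patients, 21 in all, which doubles to exactly 28:14. Responder power at 28:14 is above 99.9%. If this is the origin, the doubling is a large reserve for the responder comparison. The paragraph does not say so, however, and the only effect size it gives is for a between-group SGRQ difference. A responder reserve does not protect the t test on SGRQ change.

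**Analysis methods may help.** Statistical Analysis says that gender, age and GOLD class will be accounted for. Under an assumed prognostic correlation of 0.3, residual variance falls by 9% and power at 28:14 and 0.9 is 80.3%. That would offset a loss of roughly 9% of patients, but the correlation is an assumption and the named primary test is unadjusted. Multiple imputation can recover only what other measurements predict of a missing final SGRQ; it does not restore the full sample.

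**The base calculation may be in the full protocol.** It may, and its absence from an article is no fault. The contradiction about what was doubled and the dropout claim are both in the article's own text.

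**Conclusion.** The point holds in a limited form. The stated 80% power for about 0.9 SD on the SGRQ difference is a no-dropout figure: 0.94 SD by exact t test with all 42 patients. The claim that the 2:1 ratio and the doubling provide for dropouts is not true of that comparison. The size depends on dropout, for which the documents give no rate: from 5% to 20% assumed, power at 0.9 runs from about 74% to 66%, and the detectable effect from 0.97 to 1.06 SD. These figures assume equal loss in both arms, an unadjusted t test, and analysis of completers only.

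A reader might take 66% to 74% as the trial's probable true power. The documents do not support that. They describe dropout as possible, not as expected at some rate, so these are illustrations and not a forecast. Separately, the paragraph leaves open whether 42 is before or after doubling. The 28:14 split and the effect size attached to it make 42 the likelier final size, but the text should say so.

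**What to change.** Keep 42 patients and rewrite the paragraph so that it:

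1. states that 28:14 gives 80% power for 0.94 SD (about 0.9) with every patient evaluable;
2. gives the power at 0.9 and the detectable effect at 28:14 under a dropout rate that the sponsor chooses and states as an assumption; at 10%, for example, about 72% and 0.99 SD;
3. no longer says that the 2:1 ratio and the doubling cover dropouts for the SGRQ mean comparison, and justifies the 2:1 ratio by usability reporting alone;
4. says whether 42 is before or after doubling, and which endpoint and target the base calculation used. If that was the responder comparison, the dropout statement can stay for that comparison, named as such.

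The cost is one reworded paragraph and a slightly less favourable stated power. No patients are added, and design and analysis are unchanged.

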### Technological Study Setup

Considering proper charging and data transfer, the daily usage of multiple connected devices can be very demanding for some individuals. Thus, a selection of sensors was combined into the CAir Desk to improve usability and compliance. The CAir Desk can be placed next to the patient's bed and allows charging of all devices with a single power plug (Figure 1).

**Figure 1 figure1:**
[figure not shown]
CAir Desk with sensors.

The smartphone serves as not only the user interface to enter questionnaires and access the symptom history through the docdok app, but also a data transfer hub from the devices to the CAir database in the IBM Cloud. Patient symptoms and the environment are tracked through a home spirometer (Air Next Spirometer, NuvoAir) to capture lung function (forced expiratory volume in 1 second/forced vital capacity), a wearable physical activty tracker (Charge 3, Fitbit Inc) to report vital signs as well as the number of daily steps as a proxy for physical activity, and the microphone and camera of the smartphone (A320, 2017, Samsung Group) to acquire nocturnal cough intensity and the color of patients’ sputum as an indicator for bacterial content. Finally, the air quality and smoking behavior in the bedroom is monitored (Foobot, Airboxlab, Esch sur Alzette) through modalities like temperature and humidity, particulate matters, and volatile organic compounds in the air. This integrated approach allows the initialization, setup, and testing of all devices before the handover to the patient and thus mitigates any installations and related technical issues from the patient. To assure the on-state of the Bluetooth and WiFi hotspot channel of the smartphone, a macro app (MacroDroid, developed by ArloSoft) was enabled, triggering switch-on events after a system restart or power connection events. All unnecessary apps on the phone are suppressed by an app-blocking app (Confidant, developed by Confidant Inc.).

The CAir backend performs data collection and storage management by microservices running in the cloud (Figure 2). Patient information, device allocations, and interactions are stored in a relational database, compared to a schema-free JavaScript Object Notation object store (ElasticSearch, Lucene library) for the raw sensor data. Data are collected from the sensors in one of two ways: (1) through the third party cloud of the sensor providers and then downloaded to the CAir cloud or (2) directly from the CAir app to the CAir cloud. Patient details and daily summaries can be accessed by the study team through a web-based docdok.health physician dashboard.

**Figure 2 figure2:**
[figure not shown]
CAir data management architecture and data flow.

Further, a CAir chatbot backend was implemented using IBM cloud functions and the IBM Watson Assistant for just-in-time interactions with the patients through a chatbot frontend provided by docdok.health. Timed triggers initiate daily conversations, such as informative sessions, physical exercises, or patient feedback through the docdok app. Further, these functions scan the databases for daily activities, degrading scores of the COPD assessment test, or nonadherence to the study protocol, notifying the study team through the docdok dashboard for health care professionals to intervene. The content and logic of the chatbot conversations are implemented using the IBM Watson Assistant, which is queried by the cloud functions to manage the conversation flow between the patient docdok app and the backend.

